## Abstract

**Introduction:**

Surgery to remove the gallbladder (laparoscopic cholecystectomy (LC)) is the standard treatment for symptomatic gallbladder disease. One potential complication of gallbladder disease is that gallstones can pass into the common bile duct (CBD) where they may remain dormant, pass spontaneously into the bowel or cause problems such as obstructive jaundice or pancreatitis. Patients requiring LC are assessed preoperatively for their risk of CBD stones using liver function tests and imaging. If the risk is high, guidelines recommend further investigation and treatment. Further investigation of patients at low or moderate risk of CBD stones is not standardised, and the practice of imaging the CBD using magnetic resonance cholangiopancreatography (MRCP) in these patients varies across the UK. The consequences of these decisions may lead to overtreatment or undertreatment of patients.

**Methods and analysis:**

We are conducting a UK multicentre, pragmatic, open, randomised controlled trial with internal pilot phase to compare the effectiveness and cost-effectiveness of preoperative imaging with MRCP versus expectant management (ie, no preoperative imaging) in adult patients with symptomatic gallbladder disease undergoing urgent or elective LC who are at low or moderate risk of CBD stones. We aim to recruit 13 680 patients over 48 months. The primary outcome is any hospital admission within 18 months of randomisation for a complication of gallstones. This includes complications of endoscopic retrograde cholangiopancreatography for the treatment of gallstones and complications of LC. This will be determined using routine data sources, for example, National Health Service Digital Hospital Episode Statistics for participants in England. Secondary outcomes include cost-effectiveness and patient-reported quality of life, with participants followed up for a median of 18 months.

**Ethics and dissemination:**

This study received approval from Yorkshire & The Humber – South Yorkshire Research Ethics Committee. Results will be submitted for publication in a peer-reviewed journal.

**Trial registration number:**

ISRCTN10378861.

Strengths and limitations of this studyThis is a randomised controlled trial with randomisation taking place using a secure internet-based system to ensure allocation concealment, which will ensure that patients allocated to each group have comparable baseline characteristics.The study includes an internal pilot phase with progression to the main study dependent on a number of criteria to ensure that the study will only proceed if it is viable to do so.Participants, clinicians and other hospital staff caring for participants will not be blind to the study allocation.The criteria used to define low and moderate risk of common bile duct stones have been identified by clinicians within the study team, as there is no universal agreed definition of these terms.The study primary outcome will be derived from routine data sources, which should ensure high levels of data completeness but is reliant on timely approval of numerous applications to holders of routine data.

## Introduction

Surgery to remove the gallbladder, known as laparoscopic cholecystectomy (LC), is the standard treatment for symptomatic gallbladder disease. LC is one of the most common operations undertaken globally, and around 70 000 LC operations are performed annually in England.^1^

One potential complication of gallbladder disease is that gallstones may pass from the gallbladder into the common bile duct (CBD). Once in the CBD, they may remain dormant, pass spontaneously into the bowel or cause problems such as obstructive jaundice, cholangitis or pancreatitis. If CBD stones are found, current guidelines recommend removal either before or during LC. Therefore, patients requiring LC are assessed preoperatively for their risk of CBD stones using a combination of liver function tests (LFTs) and imaging. If the risk is high, guidelines recommend further investigation and treatment.^2–6^ Further investigation of patients at moderate or low risk of CBD stones is not standardised, and practice across the UK varies. Fewer than 10% of these patients actually have CBD stones.^2–4 6 7^ Consequently, surgeons make different decisions about investigation of the CBD; some surgeons choose to perform diagnostic imaging tests for these patients and others do not. This variation likely results in overtreatment or undertreatment, with significant risks to the patient in terms of morbidity, health-related quality of life (HRQoL) and costs to the health service.

A UK-wide audit found that a third of patients undergoing LC, irrespective of risk of CBD stones, had diagnostic imaging to test for CBD stones.^7^ This is most frequently performed with magnetic resonance cholangiopancreatography (MRCP) before admission for LC; however, some surgeons instead use intraoperative cholangiogram and other intraoperative ultrasound examinations of the CBD. MRCP produces detailed images of the biliary and pancreatic ducts, involves a 1-hour hospital visit and costs the National Health Service (NHS) about £365. MRCP can identify CBD stones but may delay LC, which can have a detrimental effect on HRQoL and can lead to increased problems with gallstones or a more complex LC.^8^ If a CBD stone is identified during MRCP, extraction is most frequently performed before LC with an endoscopic retrograde cholangiopancreatography (ERCP). The risks and mortality associated with ERCP are significant,^9^ as is the cost to the NHS (about £1600). Not having MRCP avoids these risks but can lead to CBD stones remaining after surgery, which may also cause complications. Research is needed to establish whether it is appropriate for patients at low and moderate risk of CBD stones to proceed straight to LC without imaging the CBD with MRCP.

## Methods and analysis

### Aims and objectives

The Sunflower study aims to compare the effectiveness and cost-effectiveness of preoperative imaging with MRCP versus no MRCP (hereafter called expectant management (EM)) in patients with symptomatic gallbladder disease undergoing LC who are at low or moderate risk of CBD stones. The study will test the hypothesis that EM is not inferior to MRCP with respect to hospitalisation for treatment for a complication of gallstones up to 18 months after randomisation.

The objectives are to estimate the:

Difference between groups in the proportion of participants requiring a hospital admission for treatment of a complication of gallstones in the gallbladder or CBD.Difference between groups with respect to a range of secondary outcomes, including patient-reported HRQoL, symptoms related to complications of gallstones in the gallbladder or CBD and symptoms related to complications associated with LC and, where applicable, ERCP.Cost-effectiveness of MRCP compared with EM.

### Study design

The Sunflower Study is a multicentre, pragmatic, open, randomised controlled trial with an internal pilot. The study has an embedded Qualitative Research Integrated within Trials Recruitment Intervention (QRI) to optimise informed consent and recruitment.^10^

There are two phases to the study:

Phase 1 (internal pilot): set-up and recruit from at least 36 centres by month 16 of recruitment, with integrated QRI to optimise recruitment.

Phase 2: increase the number of centres to at least 50 and continue recruitment using the methods established in phase 1, along with integrated QRI to optimise recruitment and promote adherence in new centres.

Progression to phase 2 is conditional on the study demonstrating to the funder that: (A) at least 30 centres are open and recruiting; (B) at least 1750 participants have been randomised; (C) at least 90% of participants have followed their allocated pathway; and (D) the primary outcome can be identified reliably from routine data.

### Setting

Recruitment will take place at a minimum of 50 NHS hospitals across the UK with a recruitment target of 13 680 participants over a 48-month period (figure 1).

**Figure 1 F1:**
[figure not shown]
The study schema. MRCP, magnetic resonance cholangiopancreatography.

### Study population

The target population is adults (18 years or older) with symptomatic gallbladder disease, scheduled and fit for LC as an elective or urgent procedure who are at low or moderate risk of CBD stones. Low or moderate risk is defined as CBD diameter ≤8 mm on ultrasound scan (USS), bilirubin ≤50 µmol/L and alanine transferase (ALT) less than three times the upper limit of normal (≤3 ×ULN) and/or alkaline phosphatase (ALP) ≤3 ×ULN. If the CBD cannot be visualised on USS, the patient may be recruited if no intrahepatic duct dilatation is reported.

Patients are excluded if they are unable to undergo MRCP, have evidence of empyema or perforated gallbladder requiring urgent intervention, have had a previous gastric bypass, have had a previous MRCP or endoscopic USS within the last 3 months, have had any previous ERCP or have haemolytic disease. Patients must be willing to participate in follow-up and be able to provide informed consent.

### Primary outcome

The primary outcome is any of the following:

Any hospital admission within 18 months of randomisation for treatment of a complication of gallstones whether in the CBD or gallbladder.Complications during the admission for LC for the treatment for gallstones or any readmission for complications of the LC leading to a hospital day of >2 days. Complications will include, but not be limited to, return to theatre post-LC for any cause, percutaneous radiological drainage and ERCP for non-diagnostic reasons (eg, for a bile leak). It does not include a diagnostic ERCP performed following an MRCP where CBD stones were identified.Complications during any ERCP for the treatment for gallstones. Complications will include, but are not limited to, blood transfusion post-ERCP, percutaneous radiological drainage, treatment of a perforation occurring during ERCP, acute pancreatitis and other complications leading to a hospital stay of >2 days.

This outcome will be ascertained by linking the study data with routinely collected Hospital Episode Statistics (HES) and mortality data from NHS Digital for participants recruited in England and the equivalent data sources for participants recruited in Scotland, Wales and Northern Ireland. Routine data sources contain information on care provided to all patients treated in UK NHS hospitals.^11^ The final specification of qualifying events for identifying the primary outcome from these routine sources will be developed and validated during phase 1 of the study, through comparison of routine data with events identified from review of the medical records at 90 days post-LC.

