### Interventions

The study interventions are preoperative MRCP and EM.

Participants allocated to the MRCP group will have an MRCP before the date of their listed LC. The study will make no changes to the usual hospital radiology protocols used for MRCP and will not impose any timelines for the MRCP or any subsequent interventions. If a CBD stone is found on MRCP, surgeons can manage extraction according to their usual practice. The study does not stipulate removal of identified CBD stones, and any further interventions are at the discretion of the clinician. If an ERCP is requested, it will be performed as a separate inpatient procedure before admission for LC.

Participants allocated to EM will be listed for LC without any preoperative imaging. If MRCP is carried out, for example, due to a change in a participant’s clinical circumstances after randomisation, this will be documented as a crossover.

In both groups, intraoperative imaging will not be permitted unless there is an anatomical reason to do so, or if a CBD stone is found on MRCP. Any deviations from the protocol will be recorded and monitored.

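### The primary outcome's only ERCP exclusion is mis-worded and misplaced, so planned stone-extraction admissions after MRCP could be coded as events and bias the trial towards non-inferiority

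*Protocol article*

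**What the plan says.** The Primary outcome section of the protocol article has three elements.

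- **First element:** "Any hospital admission within 18 months of randomisation for treatment of a complication of gallstones whether in the CBD or gallbladder". No exclusion is attached.
- **Second element:** complications during the LC admission or a readmission for complications of LC. It counts ERCP done for non-diagnostic reasons, such as a bile leak, and then adds: "It does not include a diagnostic ERCP performed following an MRCP where CBD stones were identified".
- **Third element:** "Complications during any ERCP for the treatment for gallstones". Here the complication is the event, not the ERCP.

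Two other sections describe the ERCP that follows a positive MRCP. The Introduction says: "If a CBD stone is identified during MRCP, extraction is most frequently performed before LC with an endoscopic retrograde cholangiopancreatography (ERCP"). The Interventions section says: "If an ERCP is requested, it will be performed as a separate inpatient procedure before admission for LC". It also leaves stone removal to the clinician's discretion.

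On coding, the Primary outcome section says: "The final specification of qualifying events for identifying the primary outcome from these routine sources will be developed and validated during phase 1". Medical records serve as the comparison for that validation.

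**The concern.** The exclusion does not fit the procedure it seems aimed at, for two reasons.

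1. **Wording.** Once MRCP has shown a stone, the usual ERCP is an extraction. The second element itself separates diagnostic from non-diagnostic ERCP, and an extraction falls on the side that is not exempt.
2. **Place.** The exclusion sits with LC complications. An ERCP in its own admission before LC is neither part of the LC admission nor a readmission after it. The element it could meet is the first, which has no exclusion.

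Whoever writes the event codes therefore has no stated rule for this admission. If it is counted, the event is produced by the allocated test. EM participants have no planned preoperative imaging, so apart from crossovers these events fall in the MRCP arm. They raise the reference risk and shrink the observed excess with EM, which favours non-inferiority.

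Intention-to-treat does not remove this, because the bias lies in the outcome definition. The analysis by pathway followed would carry the same events. Because time to first event is used, an early planned ERCP would also displace a later true complication in the same participant.

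**Working it through.** **Inputs from the Sample size section:** 13 680 participants at 1:2, so 4560 MRCP and 9120 EM; 7% risk with MRCP; margin 1.5 points (EM not above 8.5%); one-sided 2.5%; 90% power.

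**Step 1. Reproduce the plan's figure.** With unpooled variance and no allowance for dropout:

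n(MRCP) = (1.960 + 1.2816)² × 0.07 × 0.93 × (1 + 1/2) / 0.015² = 10.507 × 0.09765 / 0.000225 ≈ 4560.2

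Rounding up gives 4561, or 13 683 in total, against 13 680 stated. Power at 4560:9120 is 90.0%. The stated size is reproduced, so the same approximation is used below. It is a binary approximation to the planned survival analysis.

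**Step 2. Chance of declaring non-inferiority.** Let f be the net addition to MRCP-arm risk from counted planned ERCP admissions, after allowing for any in the EM arm. Take EM truly at the margin:

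P = Φ[(0.015 − (0.085 − (0.07 + f))) / SE − 1.96] = Φ[f / SE − 1.96]

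SE² = (0.07 + f)(0.93 − f)/4560 + 0.085 × 0.915/9120

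**Step 3. Values of f (assumed).** The article gives only an upper bound for stone prevalence (under 10%, Introduction) and no share sent to ERCP. If a proportion s of MRCP participants has such an admission and 7% of them would have had an event anyway, then f = 0.93 × s. So s = 1% gives 0.93 points and s = 2% gives 1.86 points.

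| f (points) | Extra MRCP participants with an event (f × 4560) | SE | f/SE − 1.96 | P(declare non-inferior) |
|---|---|---|---|---|
| 0 | 0 | 0.00478 | −1.96 | 2.5% |
| 0.25 | 11 | 0.00482 | −1.44 | 7.5% |
| 0.5 | 23 | 0.00487 | −0.93 | 17.5% |
| 0.93 | 42 | 0.00495 | −0.08 | 47% |
| 1.86 | 85 | 0.00512 | 1.67 | 95% |

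The chance reaches 50% at f = 0.97 points, about 44 of 4560 participants.

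**Step 4. Sensitivity to the two unknowns.** With s = prevalence × share sent to ERCP: prevalence 1% and share 25% gives 7%; 1% and 50% gives 16%; 2% and 50% gives 47%; 5% and 25% gives 64%; 5% and 50% gives 99.4%. If EM were truly at 10%, twice the margin above MRCP, the chance is 2.5% at f = 1.5 points and 15.6% at f = 2.

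**The case against.** The strongest reply is that the article does not intend to count these admissions, and much of it points that way.

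- **Meaning of the first element.** It more naturally refers to complications caused by stones, wherever the stones lie. The Aims and objectives use that sense, and the Introduction lists jaundice, cholangitis and pancreatitis as problems that duct stones cause. The Introduction does call passage of stones into the duct a complication, but of gallbladder disease rather than of gallstones.
- **Third element and Discussion.** The third element would add little if an uncomplicated ERCP already counted. The Discussion says the ERCP element is there to capture avoidable complications of overtreatment.
- **Scope of the exclusion.** It may have been meant for the whole outcome, since under the second element alone it does almost nothing.
- **Later specification.** Event coding is to be fixed and validated in phase 1, and MRCP and ERCP details are collected on the trial's own forms.

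This stands as evidence of intent. A reader might infer that every planned extraction is an event as written, that such events occur in one arm only, and that non-inferiority is forced. The documents do not support this. The first element has a more natural narrower reading, EM crossovers to MRCP are foreseen, removal is discretionary, and the ERCP share is not given.

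The reply does not repair the sentence. The exclusion is a stated rule that conflicts with the Introduction and the Interventions section. Validation against medical records cannot settle the matter either, because both sources would show the same admission. What is missing is a rule on whether it counts.

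**Conclusion.** Wrong as written, and it should be fixed. The exclusion exempts a diagnostic ERCP under the LC element, while the article describes an extraction in a separate earlier admission. The first element gives no rule for that admission, so it could be coded as a primary event against the apparent intent.

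If the admissions are not counted, there is no effect and the planned 2.5% error holds. If they are, the comparison is biased towards EM being non-inferior. At 0.25 to 0.5 net points the error at the margin is 7.5% to 17.5%, which is inflated but far from decisive. At 0.93 it is 47%, and at 1.86 it is 95%. These figures rest on an assumed number of admissions, EM truly at 8.5% v 7%, and a binary approximation to the survival analysis.

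**What to change.** Reconcile the Primary outcome section with the Introduction and Interventions sections:

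1. Replace the word diagnostic and move the exclusion so that it governs all three elements.
2. State that a planned pre-LC admission for ERCP prompted by a stone seen on imaging, with no acute gallstone complication at admission, is not in itself a primary event in either arm.
3. State that complications of that ERCP still count under the third element.
4. Carry the rule into the routine-data event specification before any comparison by arm. Identify these admissions by linking the MRCP and ERCP case-report data to the routine record, with coding blind to allocation.

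The cost is a change of outcome wording and a little more linkage and coding. No new data collection is needed, because Table 1 already lists MRCP and ERCP details.

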### Secondary outcomes

Patient-reported HRQoL will be measured using the EQ-5D-5L questionnaire.^12^ To minimise the overall study burden, about 20% of participants will be sampled and asked to complete questionnaires at multiple time points (table 1). A questionnaire pack will be provided to participants containing the validated EQ-5D-5L questionnaire plus questions about the impact of abdominal pain on work, productivity and primary healthcare use.

**Table 1 T1:** Data collection time points

Data item	Prerandomisation	Presurgery	Hospital admission for LC	90 days post-LC	3 months*	6 months*	12 months*	18 months*
Eligibility	✓							
Written informed consent	✓							
Medical history	✓							
EQ-5D-5L, productivity and primary care use questionnaire (20% sample)	✓		✓‡		✓	✓	✓	✓
MRCP, ERCP and intraoperative imaging details, if applicable		✓						
Operative and postoperative details			✓					
Items in the symptomatic gallstone core outcome set				✓				
Safety data				✓				
Study consultations audio recorded for QRI†	✓							

*These time points are months post randomisation.

†During phase 1 of the study, some recruitment consultations will be audio-recorded at high volume centres with patient consent. Thereafter, some consultations will be recorded at centres where recruitment rates fall below target.

‡Participants will not be asked to complete the LC admission questionnaires if they have completed the baseline questionnaires within the previous 2 days.

ERCP, endoscopic retrograde cholangiopancreatography; LC, laparoscopic cholecystectomy; MRCP, magnetic resonance cholangiopancreatography; QRI, Qualitative Research Integrated within Trials Recruitment Intervention.

Other secondary outcomes include items that cover the domains in the core outcome set for patients with symptomatic gallstones and hospital resource use in the 18 months after randomisation collected from routine data sources.^13 14^

### Sample size

The sample size of 13 680 has been chosen to test the hypothesis that EM is non-inferior to MRCP with respect to the primary outcome. In estimating the sample size, we have considered the proportion of patients that would be expected to experience the primary outcome, as identified in the CholeS audit (5%–10%) and through exploration of HES data.^7^ This includes patients at high risk of CBD stones. The consensus among clinicians on the study team was that the non-inferiority margin should be set at 1.5%, that is, that the risk of the primary outcome with EM should not exceed 8.5% assuming a risk of 7% after MRCP. A study of 13 680 participants will provide 90% power to test the non-inferiority hypothesis for a 7% event risk with MRCP and 80% power to test the non-inferiority hypothesis for a higher event risk of 8.5%, assuming 2.5% one-sided statistical significance and a 1:2 allocation ratio (MRCP:EM). The 20% sample of participants providing HRQoL data will be stratified by centre. This sample of 2736 participants will have >90% power to detect a small effect size of 0.12 standard deviation between groups on the EQ-5D-5L questionnaire.

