### Statistical analysis

The study will be analysed on an intention-to-treat (ITT) basis, that is, outcomes will be analysed according to the allocated treatment pathway irrespective of future management and events, and every effort will be made to include all randomised participants. Non-adherence to the treatment allocation will be documented. The primary analysis will follow the Consolidated Standards of Reporting Trials guidelines for a non-inferiority study.^15^ An analysis according to treatment pathway followed will also be performed for the primary outcome. As recommended, both analyses will be considered when assessing whether the hypothesis is met.^16^ The primary outcome will be compared using survival methods to allow for censoring. For participants without a qualifying primary outcome event, they will be censored at the time the dataset was compiled. If more than one qualifying event occurs (eg, two hospital admissions for gallstone-related complications), time to the first event will be used. The frequency of each element of the primary outcome and reasons for admission, where applicable, will be described. Secondary outcomes will be compared using a mixed model for continuous outcomes or a generalised linear regression model for binary outcomes, adjusted for prerandomisation measures when available. For secondary outcomes measured at multiple time points, changes in treatment effect with time since randomisation will be assessed by adding a treatment by time interaction to the model and comparing models using a likelihood ratio test. Model fit will be assessed, and alternative models and/or transformations (eg, to induce normality) will be explored where appropriate. Sensitivity analyses using multiple imputation for missing data will be explored. Analyses will be adjusted for centre, and treatment differences will be reported with 95% confidence intervals.

A detailed analysis plan will be prepared. There is no intention to compare any outcomes between groups at the end of phase 1; only descriptive statistics about eligibility, recruitment and adherence will be summarised at this time to determine whether the study satisfies the progression criteria.

Exploratory analyses will include:

Relationship between number and size of stones seen on MRCP and patient outcome (cohort undergoing MRCP only).Relationship between stones removed under ERCP or not (eg, ‘necessary’ vs ‘unnecessary’ ERCP) and patient outcomes (cohort undergoing ERCP only).

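### On the stated inputs, 13,680 participants give about 84% power at an 8.5% event risk, not the 80% quoted beside the correct 90% at 7%

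*Protocol article*

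**What the plan says.** The Sample size section of the protocol article states its purpose plainly: "The sample size of 13 680 has been chosen to test the hypothesis that EM is non-inferior to MRCP". It reports a clinical consensus that "the non-inferiority margin should be set at 1.5" percentage points, and illustrates this as a risk of no more than 8.5% under expectant management (EM) against 7% after MRCP.

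One sentence then gives two power figures for the same total. The study "will provide 90% power to test the non-inferiority hypothesis for a 7% event risk with MRCP", and it has "80% power to test the non-inferiority hypothesis for a higher event risk of 8.5%, assuming 2.5% one-sided statistical significance". The allocation ratio of 1:2 (MRCP:EM) closes that sentence and applies to both figures. The section gives no allowance for loss or missing outcomes, and nothing other than event risk is said to differ between the two scenarios.

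**The concern.** A reader takes the two figures as two points on one power curve: same sample size, margin, significance level and allocation, with only the event risk changed. If one point is exact and the other is about four percentage points off that curve, the sentence does not describe a single calculation.

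The second figure matters because it shows how well the design withstands a higher event risk than planned. The section itself cites an expected range of 5% to 10% for the primary outcome. As printed, power falls to 80% at a risk of 8.5%. If that point really lies higher, anyone comparing an observed overall risk of, say, 9% with this sentence would wrongly conclude that power had dropped below 80%.

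**Working it through.** **Inputs, all from the Sample size section.** Total N = 13,680, so 4,560 MRCP and 9,120 EM at 1:2. Margin 0.015 absolute. One-sided significance level 0.025, z = 1.960. Event risk p = 0.07 or 0.085. Assumption: the true risk is p in both arms, the usual alternative for a non-inferiority design.

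**Formulas.**

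SE = √[p(1−p)(1/4,560 + 1/9,120)] = √[4.5·p(1−p)/13,680]

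Power = Φ(0.015/SE − 1.960)

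N required = 4.5·p(1−p)·(1.960 + z_power)²/0.015²

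**Step 1: the plan's 90% at 7%.**
- SE = √(4.5 × 0.0651/13,680) = 0.004628.
- 0.015/0.004628 = 3.241, and 3.241 − 1.960 = 1.281, so power = 90.0%.
- N for 90% = 4.5 × 0.0651 × (1.960 + 1.282)²/0.000225 ≈ 13,681. Rounding up to whole MRCP participants gives 4,561 × 3 = 13,683.

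The stated N matches to within three participants, so this is evidently the design calculation, with no inflation for loss.

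**Step 2: the same calculation at 8.5%.**
- SE = √(4.5 × 0.077775/13,680) = 0.005058.
- 0.015/0.005058 = 2.966, and 2.966 − 1.960 = 1.006, so power = 84.3%, against 80% stated.
- N for 80% = 4.5 × 0.077775 × (1.960 + 0.842)²/0.000225 ≈ 12,209, or 4,070 × 3 = 12,210 in whole participants. That is about 10.8% fewer than 13,680.
- Solving for the risk at which 13,680 gives 80%: p(1−p) = 0.000225 × 13,680/(4.5 × 7.849) = 0.0871, so p ≈ 9.6%.

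**Step 3: could another method give both figures?** Each was run with no loss allowance.

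| Method | Power at 7% | Power at 8.5% |
|---|---|---|
| Stated in the article | 90% | 80% |
| Unpooled, equal risks (above) | 90.0% | 84.3% |
| Same, continuity-corrected | 89.4% | 83.5% |
| Farrington-Manning | 91.0% | 85.4% |
| Simulated Wald interval | 90.5% | 84.8% |
| Difference test, pooled (7% v 8.5%; 8.5% v 10%) | 86.9% | 81.1% |
| Freedman (ratio 2, same pairs) | 86.0% | 80.3% |
| Log odds ratio, equal risks | 84.1% | 78.6% |
| Schoenfeld, equal risks | 83.9% | 78.3% |

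Methods that give about 90% at 7% give 83% to 85% at 8.5%. Methods that come near 80% at 8.5% give 84% to 87% at 7%. None returns the pair.

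**Step 4: the effect of a common loss.** The document gives no loss rate, so these rates are illustrative assumptions.

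| Loss in both arms | Power at 7% | Power at 8.5% |
|---|---|---|
| 0% | 90.0% | 84.3% |
| 2% | 89.4% | 83.5% |
| 5% | 88.5% | 82.4% |
| 10% | 86.8% | 80.3% |

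No single loss rate gives 90% and 80% together. Exactly 80% at 8.5% needs a loss of about 10.8%.

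**The case against.** The strongest reply is that the error is harmless. Power at 8.5% is higher than claimed, so the 80% is met as a floor; the sample size, the margin and the design's conclusion are untouched. The figure may have been rounded down to mean at least 80%, or come from a difference-detection formula, and the full protocol may explain it.

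Most of this stands. It settles the severity, and it means the origin of the 80% cannot be known from the article. It does not remove the mismatch. The sentence lists its assumptions and presents both figures as following from them. The 90% beside it is exact, and the same section uses a greater-than sign for the quality-of-life sample, so an inequality could have been written here too.

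A reader might also infer that the trial is under-powered because 13,680 has no reserve for loss. The article does not support that. Under Primary outcome and Risk of bias, the outcome comes from linked routine data, chosen partly to limit missingness. Under Ethics and dissemination, routine data continue to be collected after withdrawal unless the participant objects. Under Statistical analysis, participants without an event are censored and those who deviate are analysed as allocated. Planning without inflation is not an error in that setting.

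**Conclusion.** The point holds as a reporting inconsistency of minor severity. On the stated inputs, with equal true risks, power is 90.0% at 7%, as claimed, and about 84% at 8.5%, about four percentage points above the figure given. The two figures do not share the one set of assumptions listed. The error is conservative, and the sample size is not too small.

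Two further inferences are tempting and should not be drawn:

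- **That the 80% must reflect a 10% loss applied to one scenario only.** This is one possible explanation. Other formulas come near 80% at 8.5% with no loss at all.
- **That the real power is lower because two analyses decide the result.** The Statistical analysis section says "both analyses will be considered when assessing whether the hypothesis is met", which is not a rule that both must succeed. Its second analysis is by pathway followed, with no stated rule excluding anyone. The requirement that "at least 90% of participants have followed their allocated pathway" is a pilot progression criterion in the Study design section, not a forecast of exclusions. A joint power of about 86% can be computed only by assuming both a both-must-succeed rule and a 10% exclusion, and the article states neither.

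**What to change.** Change one clause in the Sample size section, in one of two ways:

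1. Keep the stated assumptions and correct the second figure: 90% power at a 7% event risk and about 84% at 8.5%, or equivalently 80% at about 9.6%.
2. If the 80% rests on an unstated assumption, state it and apply it to both figures. For example, if it was a loss of about 10%, the pair becomes about 87% at 7% and 80% at 8.5%.

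The cost is one sentence. The recruitment target, the margin and the analysis do not change.
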